**Fig 1 pone.0276843.g001:**
[figure not shown]
Flow chart of the *i-MaCHeL* programme trial design.

### Randomisation

The randomisation will be performed by an independent researcher who is blinded to the identity of the preschool, preschool personnel, or study participants [36]. The random assignment of the participating preschools (n = 12) to either the intervention or control group will be conducted using the block randomisation method. Using Research Randomizer (version 4.0) computer software [35], the 12 preschools will be divided into 6 blocks of 2 and then randomly assigned each preschool within a block to one of the two experimental conditions; condition 1 = control or condition 2 = intervention.

Randomisation will be performed at the level of preschools and not on the individual level to minimise contamination. The randomisation at the preschool level can minimise the possibility that the control group participants would influence the experimental group participants and vice-versa [37]. In addition, parents and children of the control group will not be informed about the existence of the intervention programme in other preschools. Since the recruitment of the participants occurs at the preschool level, it is a very low possibility that there will be spillover effects between the intervention and control groups. However, to avoid any possibility of “contamination” between the intervention group and the control group, participants will be asked not to share or discuss the intervention-based activities with others [38].

### Blinding

The single-blind RCT will be applied in the present study, in which the researcher but not the study participants know which intervention will be allocated at the preschool level. On the other hand, participants do not know to which group they will be assigned to improve external validity [39]. The single-blind method minimises bias and ensures that subjects’ knowledge of intervention assignments may not influence their response to the intervention programme [37].

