#### Classroom component (teacher-led classroom activities)

The teacher will deliver the classroom sessions in the preschool setting (with assistance and guidance from the researcher). Classroom activities focused on fun and active activities, exercises, and cooking demonstrations. The classroom activities will be conducted every two weeks in order not to overload the teachers. Each session takes approximately 60 minutes to complete. The preschool teachers will be encouraged to implement the activities during their teaching and learning sessions. The sessions at preschool will be conducted based on the date and time provided by the preschool teacher. Therefore, discussions with preschool teachers will be held in advance to ensure the delivery of the programme is aligned with the existing preschool teaching and learning process and the standard health education curriculum. The suitable time to conduct the programme will also be discussed with preschool teachers to ensure the programme can be implemented within the allocated time without interfering with the learning time of preschool children. The appropriate time based on the existing timetable, such as during outdoor activity class time (physical activity and free play), will be considered for the programme sessions.

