### Data management

The data generated in this study are quantitative data gathered through self-administered paper-based and web-based surveys, auto-generated website usage data, and anthropometric measures. In ensuring generated data are reliable, valid, and usable, the study used validated questionnaire items and standard procedures for the anthropometric data collection. Data collection, data cleaning, and statistical analyses will be performed by members of the research team. Study staff involved in data collection and management will be trained in implementing the procedures before and during data collection or management activities.

Once eligible child-parent dyads are determined, the children’s anthropometric data (BMI) and parent data will be collected within two weeks. Teachers will distribute the sealed envelopes to preschool children to deliver to their parents. The envelopes contain a set of three-day food record booklets and a child’s physical activity questionnaires. Parents will be asked to complete the questionnaires with their children throughout the study. After completing the surveys, the parents will return the completed food record booklet and questionnaires to preschools in sealed envelopes. The surveys will be kept by head teachers and subsequently collected by researchers. The researcher will check all completed forms for completeness and accuracy. When necessary, missing information will be requested and added during the parent’s visit to the preschool or by phone call. For the web-based surveys, the force step completion function will be used to prevent missing data, so informants can only continue with the questionnaire when all items are completed [62].

Data quality and maintenance of confidentiality will be regularly monitored by the supervisors. Outcomes of this data monitoring will be summarised in an overview and reported to all research personnel. During monthly study staff meetings, outcomes of this data monitoring will be summarised in an overview and reported to all research personnel [62]. Supervisors will regularly review data collection and management procedures at study staff meetings throughout the intervention period to ensure that they follow with fidelity and address any issues or barriers to implementation.

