#### Data security and confidentiality

All data will be anonymised before entering data manually into an electronic data capture interface. All information will remain confidential and anonymised within the study team. Participant-specific data will be entered into the electronic data capture interface using only study IDs. Only the personal identifier of participants’ date of birth will be included in the database. In ensuring data quality and validity, the entered data will be double-checked by the person entering the data, and random checks will be performed regularly to ensure data validity. The statistical analyses will be conducted on anonymised data.

To anonymise the data, each participant will be assigned with a unique identification number (ID number), and no participant identifying information will be stored alongside data. The ID number with personal information will be safely stored separately from the trial data in order to secure confidentiality. Consent forms will be stored separately from participant data. The ID number will be used to administer and track all data collection, stored separately from data collection tools and locked in a secure room with limited access permissions. In ensuring the long-term preservation of the data generated in this study, the data files will be stored on secure password-protected university servers that are backed up daily, and access is restricted to researchers with passwords. Data generated via online survey software will be downloaded in spreadsheet format at least twice weekly. Data will be checked regularly to ensure the accuracy of data capture. All data will be uploaded to the password-protected university servers.

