### Statistical methods

Differences in changes over time between the intervention and comparison groups will be assessed for each outcome. General linear model repeated measure analysis will be used to determine differences between groups over time (baseline, 3-month, and 9-month) with adjustment for potential covariates. Intention-to-treat (ITT) principles will be applied for parametric data. All participants will be analysed in both intervention and control groups regardless of whether they attended all data collection time points or completed the intervention [22]. The intention-to-treat principle is useful to preserve the sample size by including all randomised respondents regardless of noncompliance or withdrawal. The principle will be used to lower the probability of reduced statistical power due to the dropouts excluded from the final analysis.

Descriptive statistics (percentages or mean ± SD) will be calculated to describe participants’ sociodemographic characteristics and scores for each outcome measured by treatment and control groups. Repeated measures Analysis of Covariance (ANCOVA) will be performed to determine significant differences between groups at the 3- and 9-month surveys. The measures analyses will be controlled for covariate variables known to influence the outcome measures (child gender, parent education level, parent age, and parent income) [22]. The significance level will be set at ≤ 0.05. Analyses will be performed using Statistical Product and Service Solutions (SPSS; version 25.0; IBM, Armonk, NY, USA).

As randomisation will be at the school (cluster) level, the primary analysis will be adjusted for the clustering effect and the baseline value of the outcomes [63, 64]. Subgroup analysis will be performed to determine the direction of intervention effects by socioeconomic status, sex, and weight status. Where appropriate, multiple imputation methods will be used to account for missing data [18].

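### The plan masks only participants and gives cleaning and analysis to the research team, so discretionary steps can be decided with the direction of effect visible; a coded file would reduce this cheaply, though not remove it

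*Protocol article*

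**What the plan says.** The protocol article defines the trial as single-blind, and under Blinding it says who is and is not masked: "the researcher but not the study participants know which intervention will be allocated at the preschool level".

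Under Data management it says who handles the data: "Data collection, data cleaning, and statistical analyses will be performed by members of the research team".

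Two other statements might be taken for masking of the analysis:
- Randomisation: "The randomisation will be performed by an independent researcher who is blinded to the identity of the preschool, preschool personnel, or study participants".
- Data security and confidentiality: "The statistical analyses will be conducted on anonymised data".

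On delivery, the Classroom component section has teachers run the sessions "with assistance and guidance from the researcher".

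On steps left to judgement:
- Statistical methods: "Where appropriate, multiple imputation methods will be used to account for missing data".
- The same section limits intention to treat to parametric data, whereas the Abstract states it without that limit.
- Data management has the researcher check returned forms and, where needed, ask parents for missing items in person or by phone.

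**The concern.** The concern is with cleaning and analysis, not with who weighs and measures the child. Masking participants does not protect decisions taken after the data are in. If the people who clean and analyse know the arms, each decision that the plan leaves to judgement can be taken while seeing which arm it helps. No ill intent is needed: a data query pursued harder in one arm, or an imputation accepted because its result looks plausible, is enough.

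At stake is the credibility of the BMI z-score comparison for the imputation and intention-to-treat decisions. For the form queries it is the parent-reported secondary outcomes, since those forms are food records and questionnaires.

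**Working it through.** No figure in the plan bears on masking, so there is none to reproduce. The check sets the statements side by side.

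**1. Who is masked.** Blinding: participants are masked and the researcher is not. Randomisation: the randomiser is masked, but only to the identity of preschools, staff and participants. No section masks an analyst.

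**2. Who handles the data.** Data management gives collection, cleaning and analysis to one group, the research team. Blinding speaks of the researcher in the singular. That these are the same people is an inference. It is a strong one, because no separate analyst appears anywhere and the researcher also supports delivery of the classroom sessions.

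**3. Whether anonymisation hides the arm.** Data security and confidentiality describes study IDs, separate storage of personal information, and date of birth as the only personal identifier kept in the database. Nothing there recodes or withholds the arm.

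**4. Whether the arm could be recovered anyway.** Statistical methods adjusts the primary analysis for clustering, so a preschool identifier must be in the analysis file. There are 12 preschools, 6 per arm. Someone who has worked with them can read the arm from an uncoded preschool name. Website-usage data, listed among the study data, and module-completion forms also point to the intervention arm.

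**5. What is left to judgement.**

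| Step | Section | Outcomes affected |
|---|---|---|
| Form checks and requests for missing items | Data management | Parent-reported secondary outcomes |
| Multiple imputation where thought appropriate | Statistical methods | Primary and secondary |
| Intention to treat for parametric data | Statistical methods | Any outcome judged non-parametric |

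For scale, the plan allows for 20% loss in 460 dyads: 0.20 × 460 = 92 dyads to which an imputation decision could apply.

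**6. What coded labels would change.** Exchanging arms A and B turns the estimated difference d into −d and the test statistic z into −z. The value |z|, and with it the two-sided p-value, is unchanged. Coding therefore blocks a choice made by direction but not a choice made by the size of p. That second route is closed only by fixing the rule and the model beforehand.

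**The case against.** **This may be an omission that the full protocol or analysis plan cures.** Imputation rules and lock procedures often sit there, and their absence from an article is no fault. If an unseen plan fixes the imputation rule, that example falls away. But the article does not stay silent on masking: it states who knows the allocation and who analyses. That part of the objection fails.

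**The text does not say that each analyst knows the arms.** This stands, and the point is worded as an inference for that reason.

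**A reader might infer a longer list of open choices.** The documents do not support it:
- The Statistical methods section does begin "with adjustment for potential covariates", but it then names four (the child's sex and the parent's education, age and income) and fixes adjustment for baseline and clustering.
- The general linear model and the repeated-measures analysis of covariance can be one model described twice.
- No section mentions outliers, and the Anthropometric measurements section fixes when a third reading is taken and which readings are averaged.

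**A reader might also put an inflated false-positive rate on this.** Under an assumed correlation of 0.9 between test statistics, taking the best of two analyses gives 7.0% instead of 5%, and the best of four gives 9.3%. Both the number of analyses and the correlation are assumptions. These figures describe selection on the two-sided p-value, which by step 6 is the same with coded labels. They do not measure what coding would gain.

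**Nor can it be said that the choices could never be checked.** The section on access plans no public release of data or code but says that researchers' requests will be supported.

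**Conclusion.** The point holds in a limited form. The plan states a design in which only participants are masked and the research team cleans and analyses the data, and neither the masked randomiser nor anonymisation hides the arm. Some discretionary steps can therefore be decided with the direction of effect visible. This rests on the inference that the analysts are among those who know the allocation.

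Its size is not quantifiable from the document. The nearest indication is the 92 dyads that planned loss would expose to the imputation decision. Sample size, power and significance level are unaffected.

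It would go too far to say that coded labels prevent selective analysis at no cost. They reduce it: p-values stay visible, 12 preschools may be recognisable by size or by children's dates of birth, and queries made at the preschool or by phone are made with the preschool known. This is a cheap improvement, not an error that invalidates the analysis.

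**What to change.** Add to Blinding and Data management text to this effect:

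- Before any analysis by arm, the imputation rule and the primary BMI z-score model are fixed in writing.
- A team member who does not run the primary analysis, such as the holder of the separately stored ID key, replaces the arm by A/B and each preschool by a random number, and holds back module-completion and website-usage data.
- Data cleaning and the primary analysis are completed and locked on this coded file, where possible by an existing team member not involved in delivery, before the code is opened.

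The independent researcher who randomises should not do the recoding: "The randomisation will be performed by an independent researcher who is blinded to the identity of the preschool", and replacing preschool names would break that masking.

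The cost is one recoding step, one paragraph of text and some care over who does what within the existing team. The gain is partial masking, and the text should say so.

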### Intervention development

The information and contents (healthy eating, physical activity, and sedentary behaviour) of the *i-MaCHeL* programme are based on the current evidence-based national guidelines and recommendation for children: Malaysian Dietary Guidelines for Children and Adolescents 2013 [40] and Recommended Nutrient Intakes for Malaysia 2017 [41]. The contents also correspond to the information provided by the Nutrition Division of the Ministry of Health Malaysia (MOH) and the ten years long-term National Plan of Action for Nutrition of Malaysia III (NPANM III) 2016–2025 [42]. The intervention group is designed based on theory-based behaviour modification intervention. The intervention group will focus on the modification of TTM, SCT, and HBM constructs. The behaviour change strategies that will be employed in the intervention materials include: 1) SCT constructs which are role modelling, goal-setting, behavioural contracting and rewards, and self-efficacy; 2) HBM constructs which are perceived susceptibility, perceived severity, perceived benefits, and perceived barriers and; 3) TTM constructs which are decisional balance, and readiness to change [43–45].

In ensuring acceptability and responsiveness to the wants and needs of the participants, the content of the *i-MaCHeL* module and website has been extensively studied by involving a multidisciplinary panel of experts in paediatric obesity, nutrition, behavioural science, physical activity, multimedia, and preschool teachers. The multidisciplinary panel of experts has been consulted regularly throughout all phases of *i-MaCHeL* development to ensure that the most current knowledge and best practices are employed in the *i-MaCHeL* programme. The parents of preschool children are also involved in several steps of the *i-MaCHeL* module development. The most common questions, comments, feedback, and recommendations by the experts and parents are confirmed as the main topics to incorporate into the already planned intervention topics for the *i-MaCHeL* module. The planned intervention topics are changed in line with the data obtained.

The usability of the interactive website of the *i-MaCHeL* programme was pilot tested among a sample of parents having characteristics similar to the eligibility criteria of the present cluster RCT study but not in the RCT study. The study participants included 42 parents of preschool children. The parents were provided with online individualised feedback to allow parents to provide feedback, comments, and recommendation to improve the intervention process of the *i-MaCHeL* programme. The questionnaires to assess the usability of the *i-MaCHeL* website were adapted from the System Usability Scale (SUS) [46]. The SUS represents a simple ten-item instrument using a 5-point Likert scale. Descriptive analyses were used to assess the usability of the *i-MaCHeL* Website. The findings of the study showed that 83.3% of the Web users agreed that the programme website was not complicated, user-friendly, and not awkward to use. The programme website appeared satisfactory to users, especially related to the storyline, content, colour schemes, subtopic arrangement, and graphics.

### Intervention group description

The *i-MaCHeL* programme consists of the website component, interactive activities, teacher-led classroom activities, social media component, and theory-based behavioural change component. The parents in the intervention group will be conducted entirely online without face-to-face meetings. The parents will complete 13 modules over a 3 months’ period (one module per week). It takes approximately 60 minutes to complete each module. Below are detailed components of the *i-MaCHeL* intervention group.

#### Website component

To offer the best user experience, the *i-MaCHeL* website has been carefully designed to be interactive and user-friendly, in which the website is: 1) easily to navigate; 2) has clear, concise, and well-formatted content (utilise headings and subheadings to breakdown content, as well as short paragraphs and bulleted lists); 3) quick load-time; 4) responsive design and mobile-friendly (mobile-optimised website); 5) well organised information and; 6) good contrast colour scheme (proper contrast between the background of the website and content).

The website consists of infographics, reading materials, educational videos, and relevant pictures of a healthy lifestyle. The compilation of helpful guides and tips related to children’s healthy lifestyle, healthy recipes for kids, and a BMI calculator will also be provided on the website. In addition, the website also consists of interactive activities. Parents will be asked to provide regular input relevant to each module by sharing healthy meals/snacks pictures, active physical activities pictures, personal ideas/experiences relating to healthy lifestyle practices, and challenges to changing the unhealthy lifestyles of their children through padlet.com (Web 2.0 platform). The quiz and interactive games using Web 2.0 platforms (such as educaplay.com, quizizz.com, and jigsawplanet.com) will also be conducted online. Besides that, the website also consists of a module completion checklist. The checklist is an online review form that should be completed by parents upon the completion of every module. The checklist allows parents to determine if they have completed all the activities or assessments in the module. The parents will also be provided with online individualised feedback. The individualised feedback allows the parents to provide feedback, comments, and recommendations to improve the intervention process of the *i-MaCHeL* programme.

#### Classroom component (teacher-led classroom activities)

The teacher will deliver the classroom sessions in the preschool setting (with assistance and guidance from the researcher). Classroom activities focused on fun and active activities, exercises, and cooking demonstrations. The classroom activities will be conducted every two weeks in order not to overload the teachers. Each session takes approximately 60 minutes to complete. The preschool teachers will be encouraged to implement the activities during their teaching and learning sessions. The sessions at preschool will be conducted based on the date and time provided by the preschool teacher. Therefore, discussions with preschool teachers will be held in advance to ensure the delivery of the programme is aligned with the existing preschool teaching and learning process and the standard health education curriculum. The suitable time to conduct the programme will also be discussed with preschool teachers to ensure the programme can be implemented within the allocated time without interfering with the learning time of preschool children. The appropriate time based on the existing timetable, such as during outdoor activity class time (physical activity and free play), will be considered for the programme sessions.

